### Implementation {16c}

The data-monitoring personnel at the university generate the allocation sequence. The enrollment of participants takes place in the rehabilitation centers, afterwards the study therapist assigns the interventions following the randomization results.

## Assignment of interventions: blinding

### Who will be blinded {17a}

Open trial, neither participants, intervention instructors, nor outcome assessors are blinded to the group assignment.

However, participants do not receive information about the study objectives, regarding whether they receive the novel intervention studied. Furthermore, the instructors do not inform participants about their risk classification and the meaning of the individualized intervention modules.

### Procedure for unblinding if needed {17b}

Does not apply

### Data collection and management

#### Plans for assessment and collection of outcomes {18a}

The reliability of the study instruments (questionnaires and functional measurements) was verified through a test-retest analysis in September 2020. The feasibility of the trial was confirmed by means of the 8-month pilot study conducted during 2019/2020 in one rehabilitation clinic in Germany.

The questionnaires are collected via the secure database portal ProWebDB®, whereby the data is forwarded directly to the security server of the University of Potsdam.

### Plans to promote participant retention and complete follow-up {18b}

After the in-person contact with the study therapist has ended (T1), the study therapist is available to the participants by telephone at fixed times during 12 weeks of the follow-up phase for any questions (until T2).

The participants are reminded by telephone at least 2–3 days before the T2 measurement to complete the online questionnaires sent by email. Two weeks before the follow-up examination at T3, the study therapist calls the test persons and reminds them of the interview.

The online access to the questionnaires (sent via e-mail) has a period of use between 14 and 21 days; afterwards, no data collection is possible. In any case, if it is not possible to complete the questionnaire online, paper questionnaires will be sent.

The close person survey also includes a reminder letter with the questionnaire at T2, in case of no response within two weeks.

### Data management {19}

The participants primarily answer the questionnaires in digital form using an online survey program (ProWebDB®). Data is collected centrally via an online system (ProWebDB®) that complies with the current General Data Protection Regulation of the European Union (DSGVO).

In the event of no internet access, computer problems, or other reasons, a copy of the questionnaire in paper is available to the study therapist. Questionnaires filled out on paper will be stored in a lockable cabinet at the university. Data on paper along with the training journal will be entered into the statistical software SPSS® by two employees, randomly checked, and followed by a plausibility check.

All the details concerning data management are stated in the statistical evaluation plan of the project.

### Confidentiality {27}

Potential participants interested in the study will be informed by the study personnel about the objectives, procedures, risks, data protection, etc. of the research project. Afterwards, they are given enough time to consider whether they wish to participate in the study. In case of voluntary participation, a declaration of consent must be signed. The written consent (informed consent) includes a declaration of consent for voluntary participation in the study, for (pseudonymized) data processing, and a release of medical confidentiality to authorize medical personnel (e.g., doctors or therapists) the disclosure of information for the study.

After consent for voluntary participation in the study, participants are assigned a specific pseudonymous code, which serves to ensure the pseudonymization of the data during the data collection period.

The original informed consent forms and the pseudonymous code sheets are collected by the study staff on site. These two documents are used to enter the name, code, address, telephone number, and survey status of study participants into a digital patient identification list. The pseudonymized code sheets will be irrevocably destroyed by the study staff as soon as the transfer to the patient identification list has been completed. The original informed consent forms are stored separately from the research data in a locked cabinet in the rehabilitation center data before being locked in the room cabinets at the university.

The patient identification list is confidential; password-protected, with restricted access only to the project manager; and stored separately from the research data on a security server of the university. If a study participant withdraws the previously given consent, they will be irrevocably deleted from the patient identification list.

Information about the traceability of personal data is only kept during the period of the study by the patient identification list. All data and documents that contain both personal data and coding together are irrevocably deleted after the completion of data collection. Since the patient identification list is irrevocably deleted immediately after the end of the data collection (after T3), a later assignment of the name of a person and the corresponding individual data is not possible.

Due to the early pseudonymization of the data at the first measurement time (T0), all data is only collected in a coded form. The study staff deals exclusively with coded data, which does not allow for individual conclusions about the study participants. All electronic data will be stored exclusively on the university security server at the end of the project. All pseudonymized coded research data will be stored at a security server.

### Plans for collection, laboratory evaluation, and storage of biological specimens for genetic or molecular analysis in this trial/future use {33}

If no basic physiological status information is recorded during the initial medical examination, the willingness to take a blood sample and store it for subsequent analysis is requested at the clinic check-in with the corresponding informed consent.

## Statistical methods

### Statistical methods for primary and secondary outcomes {20a}

Data is analyzed at the end after T3 data collection completion. Then, an examination of underlying assumptions for parametric or non-parametric hypothesis testing is applied. For the primary outcome pain (DISS, CPI), an analysis of variance (ANOVA) repeated measures for three time points (T0, T2, T3) between the groups (intervention vs control group) with covariates adjustment is planned. The covariates to include in the analysis are center, age, and sex. A complete case analysis is intended.

For secondary outcomes (psychometric items), missing value imputation follows only (in case of psychometric scores) the specific test manuals. Likewise, variance analytical testing is proposed. A sensitivity analysis is planned for concomitant therapy, such as medications.

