#### Primary outcomes

##### Chronic pain

The study has 2 co-primary outcomes (Characteristic Pain Intensity and Disability Score).

*Chronic pain* is assessed by the German version of the Chronic Pain Grade Questionnaire (CPG) [33, 34], which comprises two subscales: characteristic pain intensity (CPI: 0 = “no pain” to 100 = “pain as bad could be”) and disability score (DISS: 0 = “no disability” to 100 = “unable to carry on any activities”) from the past 3 months. Both subscales consist of the mean of three individual Numeric Rating Scales ranging from 0 to 10, showing good internal consistency (Cronbach’s alpha 0.88 and 0.68, respectively, from the literature [34]). Furthermore, these subscales display moderate to high relations to other instruments measuring a patient’s disability. Therefore, the CPG questionnaire is a reliable and valid instrument when an uncomplicated grading of chronic pain severity is required [34]. The CPG is administered at all time points (T0, T1, T2, and T3). The main time point is T2.

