### Sample size {14}

For the main study, the sample size calculation was based on a small effect size of *d* = 0.2 as well as assumptions on the normal distribution and variance equality. Alpha-error probability of 5%, beta-error probability of 20%, and a ratio allocation of 1:2 (control vs intervention) were considered. The repeated measures ANOVA for three time points between the groups with a correlation among repeated measures of 0.57 (results from pilot study, unpublished material, based on CPG Disability score) calculate a sample size of 843 (*n* = 562 in the intervention and *n* = 289 in the control group). Assuming a dropout rate of 30%, the total number of participants to be included in the study is *N* = 1204 (power analyses by G*Power; Faul, Erdfelder, Lang & Buchner, 2007) [56].

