### Methods for additional analyses (e.g., subgroup analyses) {20b}

We also plan a subgroup analysis comparing the multimodal and the unimodal group, with the control group. In these cases, using a repeated-measures ANOVA between the two groups mixed with covariates such as age, sex, and baseline pain is planned for each multimodal and unimodal group.

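### The primary repeated-measures ANOVA is not tied to the declared main time point T2, its tested term is not named, and the term used for sizing averages in the pre-treatment T0

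*Protocol article*

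**What the plan says.** Under Primary outcomes, Chronic pain, the protocol article names two co-primary outcomes, Characteristic Pain Intensity (CPI) and Disability Score (DISS), measured at T0 to T3, and states "The main time point is T2".

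Section {20a} plans, for both, "an analysis of variance (ANOVA) repeated measures for three time points (T0, T2, T3) between the groups (intervention vs control group". The covariates are centre, age and sex, and the analysis is of complete cases. No contrast at T2 is given, and the term to be tested is not named.

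Section {14} sizes the trial with d = 0.2 and "The repeated measures ANOVA for three time points between the groups with a correlation among repeated measures of 0.57". It also states "Alpha-error probability of 5%, beta-error probability of 20%, and a ratio allocation of 1:2 (control vs intervention) were considered". The result is 843 evaluable patients, with 562 in the intervention arm, raised to 1204 for 30% dropout.

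For the unimodal and multimodal comparisons, section {20b} describes an analysis "using a repeated-measures ANOVA between the two groups mixed with covariates such as age, sex, and baseline pain is planned", without listing time points.

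**The concern.** A repeated-measures ANOVA with two groups and three visits offers two tests of treatment. The group main effect compares the groups on the average of T0, T2 and T3. T0 is taken at clinic admission, before treatment, so it contributes an expected zero with one third of the weight, and T3 takes another third. The group-by-time interaction asks whether the group difference changes across the three visits. It is a 2-df omnibus test that treats T2 and T3 alike.

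Neither test answers whether the groups differ at T2. If the main effect is used, a null result could come from the dilution rather than from the programme. If the interaction is used, a positive result could come from T3 alone. With the term left open, the choice between two tests of very different power could also be made after the data are seen.

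**Working it through.** **Inputs.** From {14}: d = 0.2 (f = 0.1 for two groups), alpha 5%, power 80%, allocation 1:2, m = 3 visits, rho = 0.57, 843 evaluable with 562 in the intervention arm. The control arm is taken as 843 − 562 = 281. The article prints 289, which would sum to 851; using 289 moves the 58% below only to 58.7%. Assumptions: SD 1 at each visit, compound symmetry, two-sided 5%, no gain from centre, age and sex.

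**Reproducing the sample size.** Between-factors formula: λ = f²·N·m / (1 + (m − 1)·rho).
- With N = 562: λ = 0.01 × 562 × 3 / 2.14 = 7.88, power 0.8001. So 562 is the total for two equal groups of 281.
- 562 × 1.5 = 843, so the 1:1 total was reused as the intervention arm.
- 843 / 0.7 = 1204.3, which matches 1204.

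Candidates that do not give 843:
- the within-between interaction at f = 0.1: 140;
- the same main effect sized directly for 2:1: 630;
- a plain two-sample comparison at one visit with 2:1: 885.

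**Power of the main effect.** The variance of a patient's three-visit mean is (1 + 2 × 0.57)/3 = 0.713. SE = √(0.713 × (1/562 + 1/281)) = 0.0617.

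**Power of the interaction.** λ = Σ(dₜ − mean d)² / [(1 − 0.57)(1/562 + 1/281)] on 2 df. For (0, 0.2, 0.2), the sum of squares is 0.0267 and λ = 0.0267 / (0.43 × 0.00534) = 11.6.

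| True d at T0, T2, T3 | Mean d | Main-effect power | Interaction power |
|---|---|---|---|
| 0.2, 0.2, 0.2 (sizing assumption) | 0.200 | 90% | 5% |
| 0, 0.2, 0.2 | 0.133 (z = 2.16) | 58% | 87% |
| 0, 0.2, 0.1 | 0.100 | 37% | 76% |
| 0, 0.2, 0 | 0.067 (z = 1.08) | 19% | 87% |

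The interaction's λ depends only on the spread of the three differences. An effect at T3 only, (0, 0, 0.2), has the same spread as an effect at T2 only and therefore also 87% power. To reach 80% with the main effect under (0, 0.2, 0.2), about 1419 evaluable patients would be needed.

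**A T2 contrast in the same 562 and 281 patients, d = 0.2:**
- unadjusted: 78%;
- change from T0: 84%;
- adjusted for T0: variance 1 − 0.57² = 0.675, SE = √(0.675 × 0.00534) = 0.0600, z = 3.33, power 91%.

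**Sensitivity to rho from 0.3 to 0.7.** Main effect under (0, 0.2, 0.2): 71% falling to 53%. T0-adjusted T2 contrast: 82% rising to 97%.

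**The case against.** The strongest reply is that {20a} names a within factor and a between factor but not the tested term. With T0 as a repeated level, the interaction is the usual test of differential change. T0 is then the reference and dilutes nothing, and power is about 87%, close to the 91% of a T0-adjusted T2 contrast. On that reading the trial is larger than its d = 0.2 requires. This stands. A reader might infer that the trial's true power is 58% instead of 80%, but the article does not support that as a flat statement. The sizing formula points to the main effect but does not establish which term will be tested. The 58% also assumes that the effect persists in full to T3. And 80% is the wrong comparator, because the plan's own assumption gives about 90% at 562 and 281.

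A second reply is that the term and the contrast may be set out in the statistical evaluation plan mentioned in {19}, which is not shown. That would excuse silence. It does not remove the mismatch in the article itself, which names T2 as the main time point and then fixes a model, visits and covariates whose overall tests do not isolate T2.

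A reader might also infer that the subgroup model in {20b} uses baseline pain as both response and covariate. The section lists no visits, so this follows only if T0, T2 and T3 are carried over from {20a}. Omitting the baseline score from the primary covariates is a consequence of treating T0 as a response, not a separate error.

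**Conclusion.** The concern holds in a conditional form. The stated primary analysis does not isolate T2 under either reading, and the reading is left open.
- If the group main effect is the test, power for d = 0.2 at T2 and T3 is about 58%, and 19% if the effect is at T2 only, against about 90% under the sizing assumption.
- If the interaction is the test, power is about 87% for either pattern, but it is equally 87% for an effect at T3 only. It cannot say whether T2 differs, and the trial was sized for a different test.

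The figures are per outcome. They rest on 562 and 281 completers, rho 0.57, compound symmetry and no gain from covariates. The 0.57 comes from pilot data on the Disability Score, so its use for CPI is an assumption. The dilution of the main effect and the interaction's inability to single out T2 do not depend on the exact value of rho. Because this is the primary test of the trial, it should be settled before the data are analysed.

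**What to change.** - **{20a}:** for CPI and DISS, make the primary test the group difference at T2 adjusted for the T0 score, centre, age and sex. This can be an ANCOVA, or a mixed model with T2 and T3 as responses and T0 as a covariate. Report the T3 difference from the mixed model, or from the same ANCOVA at T3, as secondary. T1 need not be added as a response.
- **{14}:** restate the calculation for that contrast with the 2:1 allocation, and reconcile the arm sizes with the total of 843. The planned 843 evaluable patients give about 91% power per outcome at d = 0.2 and rho 0.57.
- **{20b}:** state that T0 is a covariate only and not also a repeated response.

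The cost is rewording and a modest change of model, with no new data and no more patients. The article plans the analysis after T3 collection is complete and has no interim analysis, so the change can be made before the data are analysed.

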**Methods:**

The aim of this study is to implement an individualized therapy and aftercare program within the rehabilitation offer of the German Pension Insurance in the area of orthopedics and to examine its success and sustainability in comparison to the previous standard aftercare program.

The study is a multicenter randomized controlled trial including 1204 patients from six orthopedic rehabilitation clinics. A 2:1 allocation ratio to intervention (individualized and home-based rehabilitation aftercare) versus the control group (regular outpatient rehabilitation aftercare) is set. Upon admission to the rehabilitation clinic, participants in the intervention group will be screened according to their psychosocial risk profile. They could then receive either unimodal or multimodal, together with an individualized training program. The program is instructed in the clinic (approximately 3 weeks) and will continue independently at home afterwards for 3 months. The success of the program is examined by means of a total of four surveys. The co-primary outcomes are the Characteristic Pain Intensity and Disability Score assessed by the German version of the Chronic Pain Grade questionnaire (CPG).

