### Objectives {7}

This is a study on rehabilitation aftercare for back pain patients.

The aim of the study is to evaluate whether and how well an individually tailored rehabilitation aftercare program for back pain patients works. The following hypotheses are going to be examined:
An individualized and home-based aftercare program is more effective than regular outpatient rehabilitation aftercare in terms of pain reduction.An individualized and home-based aftercare program is more effective than regular outpatient rehabilitation aftercare in terms of work ability.An individualized and home-based rehabilitation aftercare leads to better patient compliance and more sustained intervention effects than regular outpatient rehabilitation aftercare.An individualized and home-based rehabilitation aftercare could be implemented and incorporated long term (feasibility) in the regular rehabilitation aftercare routines of the German Pension Insurance.

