### Participant timeline {13}

The main outcome of interest is pain measured as Characteristic Pain Intensity and Disability Score. The trial is divided into three phases: [1] 3 weeks stay in rehabilitation, [2] 9 weeks of supervised aftercare home training (training support by phone and digital media assistance), and [3] 12 weeks of independent aftercare home training. As shown in Fig. 4, measurements will take place at four time points in each group, at baseline (T0), directly before leaving the rehabilitation stay (T1), after 9 weeks of supervised aftercare home training (T2), and after 12 weeks of independent aftercare home training (T3).

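### Hypothesis 3 claims more sustained effects, but the repeated-measures ANOVA stated for CPI and DISS tests neither what remains at T3 nor the change from T2 to T3

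*Protocol article*

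**What the plan says.** Objectives {7} lists as hypothesis 3 that the individualised home-based aftercare "leads to better patient compliance and more sustained intervention effects than regular outpatient rehabilitation aftercare". The abstract (Methods) gives the study aim as implementing the programme and "to examine its success and sustainability in comparison to the previous standard aftercare program".

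Statistical methods {20a} states the analysis of the two co-primary scores, DISS and CPI, as an analysis of variance: "repeated measures for three time points (T0, T2, T3) between the groups (intervention vs control group) with covariates adjustment is planned". The covariates are center, age and sex. It does not say whether the group term or the group-by-time term is the deciding test. For secondary outcomes, the same section adds only: "Likewise, variance analytical testing is proposed". Methods for additional analyses {20b} compares the unimodal and multimodal groups with control, again "using a repeated-measures ANOVA between the two groups mixed with covariates such as age, sex, and baseline pain is planned".

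The Outcomes section, under Chronic pain, says: "The main time point is T2". T3 comes 12 weeks later, after the independent training phase (Participant timeline {13}). None of these sections names a between-arm contrast at T3 or for the change from T2 to T3.

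**The concern.** A claim of more sustained effects concerns what is left at T3, or how much is lost between T2 and T3. The two terms of the stated ANOVA ask other questions:

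- **Group by time:** is the arm difference the same at T0, T2 and T3? With the arms equal at T0 by randomisation, any difference at T2 makes this null false, including one that has gone by T3.
- **Group:** does the average of the three scores differ between arms? A difference at T2 alone shifts that average.

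So neither term separates an effect that is kept from one that is lost. Sustainability is part of the stated aim, and Dissemination plans {31a} says the programme could enter regular aftercare if successful. If the stated analysis is all there is, the durability part of hypothesis 3 has no test that can answer it. The T2 comparison and its power are not affected.

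**Working it through.** **Inputs.** From Sample size {14}: d = 0.2, alpha 5%, three time points (m = 3), correlation ρ = 0.57, total 843, 562 in the intervention arm. The printed control arm of 289 does not fit, since 562 + 289 = 851. I use 281 (843 − 562) and give 289 as a check. Assumptions of mine: compound symmetry, SD 1, equal arms at T0, and no gain from covariates.

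**1. The plan's own figure.** For the group term with two equal arms, f = d/2 = 0.1 and

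λ = f²·N·m / (1 + (m−1)ρ) = 0.01 × 562 × 3 / 2.14 = 7.88,

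which gives 80.0% power at N = 562, or 281 per arm. Doubling the intervention arm gives 562 + 281 = 843, and 843/0.7 = 1204.3, the printed 1204. The within/interaction formula with the same f gives 140 (210 after multiplying by 1.5). The planning figure therefore matches the group term.

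**2. Group by time.** Let h = 562 × 281/843 = 187.33, and let the arm differences at T0, T2, T3 be (0, a, b). Then

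λ = h·Σ(δ − mean δ)² / (1 − ρ), with Σ(δ − mean δ)² = (2/3)(a² + b² − ab).

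- Lost, b = 0: the sum is (2/3)a².
- Kept, b = a: the sum is again (2/3)a².

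The two cases give the same λ for any a, ρ or sample size. With a = 0.2, λ = 187.33 × 0.02667/0.43 = 11.62 on 2 and 1682 df.

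**3. Group term.** λ = h·(mean δ)² / ((1 + 2ρ)/3), and (1 + 2ρ)/3 = 0.7133.

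- Lost: mean δ = 0.0667, λ = 187.33 × 0.004444/0.7133 = 1.17.
- Kept: mean δ = 0.1333, λ = 187.33 × 0.01778/0.7133 = 4.67.

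**4. Rejection rates, 562/281, noncentral F.**

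| Effect at T2, T3 (SD) | Group by time | Group |
|---|---|---|
| 0.2, 0 (lost) | 87.2% | 19.0% |
| 0.2, 0.1 (half kept) | 75.6% | 36.7% |
| 0.2, 0.2 (kept) | 87.2% | 57.9% |

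A simulation of 4000 trials of the first row gave 87.1% and 19.1%. With 562/289, group by time gives 87.8% in the first and third rows, and the group term gives 19.3% and 58.6%.

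**5. Sensitivity of the 87.2%.** ρ from 0.3 to 0.8 gives 66% to 99.6%. An effect at T2 of 0.1 to 0.3 SD gives 31% to 99.8%. The level moves a great deal; the equality of lost and kept does not.

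**6. Contrasts that address the question (562/281, normal approximation).**

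- T3 difference adjusted for T0: SE = √((1 − 0.57²)/187.33) = √(0.6751/187.33) = 0.0600. It rejects in 5% of trials if the effect is lost and about 91% if 0.2 SD is kept (0.2/0.0600 = 3.33).
- Arm difference in T2-to-T3 change: SE = √(2 × 0.43/187.33) = 0.0678. It rejects in 5% if the effect is kept and about 84% if 0.2 SD is lost, in the adverse direction (0.2/0.0678 = 2.95).

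**The case against.** The strongest reply is that {20a} assigns the ANOVA to the primary pain outcome, which is hypothesis 1, and never says that a significant F will count as evidence of durability. On that view only an omission is left, and follow-up contrasts usually belong in the analysis plan. Data management {19} mentions a statistical evaluation plan, which is not at hand and may contain such a contrast. Part of this stands: the document does not state the misuse, so the point is a mismatch between a stated hypothesis and the analysis stated for its outcomes. It is more than an omission, because the article fixes an analysis and that analysis cannot answer the question.

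Four stronger readings are tempting and are not supported:

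- **That durability would be wrongly claimed 87% of the time.** When the effect is lost by T3, the ANOVA nulls are still false, because the arms differ at T2. The 87% and 19% are power against those nulls, not inflated alpha.
- **That group by time is the planned test.** {20a} names no term. Its phrase about comparison between the groups and the sample-size formula point to the group term, where the figure for a lost effect is 19%.
- **That this ANOVA is the only use of T3.** T3 can also enter the secondary and subgroup analyses, and compliance and acceptance items are collected at T2 and T3. Patient compliance and acceptance even defines a sustainability construct, but it covers confidence in continuing the programme and barriers to doing so, not pain or disability between arms.
- **That a T3 difference alone shows a more sustained effect.** It would be significant in about 91% of trials when both arms change equally from T2 to T3. A remedy has to keep the two claims apart.

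**Conclusion.** The concern holds in this form: the analysis stated for CPI and DISS does not test the sustained-effects part of hypothesis 3, and no other stated analysis isolates T3 or the T2-to-T3 change for these scores. Under compound symmetry, the group-by-time term has the same power for a wholly lost and a wholly kept effect, about 87% each on the plan's inputs. The group term does differ, 19% against 58%, but its null concerns an average that includes baseline and T2. The percentages depend on 0.2 SD at T2, ρ = 0.57 and roughly 843 patients analysed; the mismatch of null hypotheses does not. It should be corrected before the data are analysed, but it does not touch the T2 comparison or the compliance half of hypothesis 3.

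**What to change.** State in {20a} that the sustained-effects part of hypothesis 3 is not judged by the omnibus ANOVA terms, and add:

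1. The test is the baseline-adjusted intervention-minus-control difference at T3 for CPI and DISS, with its 95% CI and the planned covariates (center, age, sex).
2. The arm difference in T2-to-T3 change is reported beside it, with its 95% CI.
3. A *sustained* benefit is claimed only if the T3 interval excludes zero in favour of the intervention.
4. A *more sustained* benefit is claimed only if, in addition, the interval for the T2-to-T3 contrast excludes zero in favour of the intervention.

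This needs a few lines of text and no further visits or patients. The cost is that durability becomes harder to claim. The planned numbers serve the T3 contrast well (about 91% power if 0.2 SD is kept). The stronger claim needs the arm difference to grow after T2, by 0.2 SD for about 84% power on that contrast. If the arms change equally, its interval excludes zero in the favourable direction in only 2.5% of trials (half of the two-sided 5%).

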### Methods in analysis to handle protocol non-adherence and any statistical methods to handle missing data {20c}

Intention to treat analysis will be performed. Per-protocol analysis is going to be applied to compare the results in a sensitivity analysis.

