### Adverse event reporting and harms {22}

The contact persons in case of such an event are both the study therapist and the corresponding physician in the clinic during the center-based phase (T0–T1) or the physician in the respective follow-up center (T2–T3). If the study therapist has been informed first about the adverse event, he/she immediately informs the physician. It is always the treating physician who decides whether to exclude the patient from the study.

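### The co-primary analysis is fixed as complete-case with 30% expected dropout: about 361 of 1204 randomised patients are left out, some with an observed T2 score, and no sensitivity analysis for missing primary outcomes is named

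*Protocol article*

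**What the plan says.** Section {20a} plans, for both co-primary scores (pain intensity and disability), a repeated-measures ANOVA at T0, T2 and T3 comparing intervention with control, adjusted for center, age and sex. It then states: "A complete case analysis is intended". Imputation appears only for psychometric scores among the secondary outcomes, following the test manuals.

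Section {20c}, whose heading covers missing data, states: "Intention to treat analysis will be performed". It adds: "Per-protocol analysis is going to be applied to compare the results in a sensitivity analysis". Section {20a} names one more: "A sensitivity analysis is planned for concomitant therapy, such as medications". The Discussion mentions sensitivity analyses for covariates. None of these concerns missing primary outcomes.

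Section {14} has the planned model "calculate a sample size of 843", and continues: "Assuming a dropout rate of 30%, the total number of participants to be included in the study is" 1204. Section {12} has the questionnaire answered at T0, T1, T2 and T3 and makes T2 the main time point.

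On adverse events, section {11b} speaks of a decision to stop the intervention. Section {22} says: "It is always the treating physician who decides whether to exclude the patient from the study".

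**The concern.** A complete case for this ANOVA needs all three scores. A patient who answers at T2 but not at T3 is deleted, so data observed at the main time point are discarded. Raising the sample from 843 to 1204 protects power, but does nothing about bias if the patients who remain are no longer comparable between arms.

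Different missingness by arm is plausible. The trial is open, and the arms ask different things of patients: supervised sessions followed by weeks of independent home training in one, group aftercare or no aftercare in the other. If the patients lost differ in pain, and differ in another way or number in each arm, randomisation no longer protects the comparison and the nominal 5% error rate does not hold. With no missing-data sensitivity analysis named, the report would not show how far the result depends on this.

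**Working it through.** **Stated figures.** 843 / (1 − 0.30) = 1204.3, which agrees with 1204. Patients left out: 1204 × 0.30 = 361, leaving 843. The arm sizes printed in section {14}, 562 and 289, sum to 851. At 2:1, 843 splits into 562 and 281, which is used below.

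**Which ANOVA term was powered.** For the between-group effect, λ = N f² m / (1 + (m − 1)ρ), with f = d/2 = 0.1, m = 3 and ρ = 0.57. For N = 562 in equal arms, λ = 562 × 0.01 × 3 / 2.14 = 7.88, which gives 80% power. The number 562 is the stated intervention-arm size, and 562 × 1.5 = 843. So the sample size fits the group main effect averaged over T0, T2 and T3. Section {12}, however, makes T2 the main time point, so three versions of the comparison are shown.

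**Standard errors in SD units, 562 against 281 completers.** √(1/562 + 1/281) = 0.0731.
- Group main effect: √((1 + 2 × 0.57)/3) × 0.0731 = 0.0617
- T2 adjusted for T0: √(1 − 0.57²) × 0.0731 = 0.0600
- Mean of T2 and T3 minus T0: √(1.57/2 + 1 − 2 × 0.57) × 0.0731 = 0.0587

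**Assumed scenarios.** No true effect, 803 and 401 randomised, correlation 0.57 throughout, 30% dropout in each arm. Dropout is random in control and rises with T1 or T2 pain in the intervention arm, at log-odds 0.5 or 1.0 per SD. The documents give no arm-specific dropout, so all of this is assumption. Bias b comes from simulation (about 3000 to 4000 trials per scenario; negative favours the intervention). The false-positive rate is Φ(|b|/SE − 1.96) + Φ(−|b|/SE − 1.96), set beside the simulated rate. Ranges span repeated runs.

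| Comparison | Dropout follows | Log-odds | Bias (SD) | Formula | Simulated |
|---|---|---|---|---|---|
| Group main effect | T1 | 0.5 | −0.082 | 26% | 27% |
| | T1 | 1.0 | −0.145 | 65% | 65–69% |
| | T2 | 0.5 | −0.104 | 39% | 38–39% |
| | T2 | 1.0 | −0.181 | 83% | 84–87% |
| T2 adjusted for T0 | T1 | 0.5 | −0.037 | 9% | 9% |
| | T1 | 1.0 | −0.065 | 19% | 19–20% |
| | T2 | 0.5 | −0.097 | 37% | 37–39% |
| | T2 | 1.0 | −0.176 | 83% | 84–86% |
| Change from baseline | T1 | 0.5, 1.0 | 0.00 | 5% | 5% |
| | T2 | 0.5 | −0.029 | 8% | 8% |
| | T2 | 1.0 | −0.054 | 15% | 16–17% |

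For scale, the design effect is 0.2 SD.

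**Other patterns, dropout following T2 pain, group main effect.**
- Same slope and same rate in both arms: 4% to 5%.
- Dropout unrelated to pain, even at 35% against 20%: about 5%.
- Slope 0.5 in both arms, with 35% against 20% dropout: about 14%.
- Slope 0.5 in the control arm only: bias +0.10 SD, against the intervention.

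**Using the observed scores.** Suppose T3 is missing depending on observed T2 pain, in the intervention arm only. The T2 comparison adjusted for T0 then gives these false-positive rates:
- Log-odds 0.5: 38.6% in complete cases, 5.6% with every observed T2 score.
- Log-odds 1.0: 84.5% in complete cases, 4.8% with every observed T2 score.

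At T3 with log-odds 0.5, complete cases give 8.6% and a likelihood analysis of all observed data gives 4.8%.

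**The case against.** The strongest reply is that section {20c} contrasts intention to treat with per-protocol, that is, allocation with adherence. Completers analysed as randomised are then an incomplete form of intention to treat and not its negation. That stands: a reader might infer a flat contradiction, but the texts support only a modified intention-to-treat analysis.

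A reader might also infer that an ineffective intervention will tend to look effective. The documents do not support this. They give no dropout by arm. Telephone contact and reminders are offered to participants in general ({11c}, {18b}), and questionnaires can be completed on paper, so a patient who stops training may still answer. Some control patients receive no aftercare, so selective loss there is equally arguable and would bias the other way.

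The figures depend on the comparison chosen, and the largest belong to a group effect that averages in the baseline score. The near-nominal error rates with all observed data are built in, because dropout was made to depend on observed pain. Such a model does not by itself remove bias when dropout depends on unobserved values.

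Leaving T1 out of the effect model is defensible. The questionnaire looks back 3 months, T1 comes about 3 weeks after T0, and it precedes home aftercare.

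Finally, section {22} does not say that outcome collection ends when a patient is excluded. Counting it as a further source of missing data would be inference.

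None of this changes the stated rule, the deletion of observed T2 scores or the lack of a named sensitivity analysis. A statistical plan not shown here might add one, but the article itself fixes the complete-case rule.

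**Conclusion.** The point holds as a criticism of a stated analysis rule. About 361 of 1204 randomised patients (30%) would leave the co-primary analysis, some of them with T2 observed. The loss of patients follows directly from the protocol's own figures.

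The bias is conditional: dropout must be related to pain, and that relation or the dropout rate must differ by arm. Its direction is unknown. Its size ranges from nothing to about 0.18 SD in the scenarios above, according to which score drives dropout and which comparison is tested. No single false-positive rate should be quoted as the trial's error rate. The case for changing the rule does not depend on one, because the complete-case rule discards observed scores at the main time point and the alternative is cheap.

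**What to change.** In section {20a}, replace the complete-case sentence with this rule: all randomised patients are analysed in their allocated arm, with all available T2 and T3 scores in a mixed model adjusted for T0, center, age and sex, and the T2 difference is the main contrast. T1 serves only as auxiliary information for missing data, for example in multiple imputation, and does not enter the averaged treatment effect. Patients with neither T2 nor T3 contribute only through such a step.

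In section {20c}, add the complete-case analysis and a delta-adjusted (missing-not-at-random) analysis as sensitivity analyses, beside the per-protocol analysis.

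Reconcile sections {11b} and {22} on whether excluding a patient from the study means stopping the intervention or also ending outcome collection. The answer determines which later scores count as missing.

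The cost is protocol wording and slightly more analysis work. No interim analysis is planned and analysis follows completion of T3, so the change can be made before results are seen. The downside is reliance on missing at random, which the delta-adjusted analysis is there to test.
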